### Aim, objectives and hypotheses

The overall study aim is to evaluate, in a randomised controlled trial, the clinical effectiveness of FGM compared to SMBG for adolescents with T1D and a history of suboptimal glycaemic control. The primary objective is to investigate the effectiveness of FGM compared to SMBG in reducing HbA1c (i.e., the primary analysis will be on a modified intention to treat basis, using all available data).

The secondary objectives are to investigate:the effectiveness of FGM compared to SMBG in increasing glucose monitoring behaviour during the 6-month trial period;the effectiveness of FGM compared to SMBG in changing disease specific and generic HRQoL, fear of hypoglycaemia, and treatment satisfaction during the 6-month trial period;acceptability and feasibility of using FGM to self-monitor glucose levels during the 6-month trial period; andAdverse events (e.g. skin problems, diabetic ketoacidosis, severe hypoglycaemia) during the 6-month trial period.

The tertiary objectives are to explore:all of the primary and secondary analyses using participants from the FGM group who scanned at least once per day 12 days out of 14 in the two weeks prior to the 6 month study visit (which is a definition modified from a recent landmark CGM study [35]) and excluding any participants from the SMBG group who used FGM at any time during the study (i.e., a per protocol analysis with potential confounding by characteristics associated with compliance, although all participants in the study have a recent history of suboptimal glycaemic control and so are likely to have similarly low baseline rates of SMB testing)the impact of FGM compared to SMBG on sleep and physical activity during the 6-month trial period; andall study outcomes in both groups at 12 months, including estimating within-group changes in the FGM group from 6 months to 12 months (to investigate persistence of changes) and within-group changes in the crossed over group from 6 months to 12 months (to see if any such changes are consistent with those in the FGM group from baseline to 6 months).

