## Methods

### Study design

Managing Diabetes is a ‘Flash’ is a two phase study programme consisting of a multi-centre randomised, parallel-group study consisting of a 6-month comparison between SMBG and FGM, including a 6-month continuation phase (see Fig. 1). Once enrolled, the total study period is 12 months for each participant (12 months of FGM for the intervention group will enable an investigation of sustained FGM outcomes). During the continuation phase, the FGM group will continue the intervention for a further 6 months and the control group will cross over and receive a 6-month FGM intervention. The primary purpose of offering FGM to the control group at 6 months is to encourage retention and engagement.

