### Sample size

Based on our data from an earlier study in this population, the standard deviation of HbA1c amongst those with values 75 mmol/mol (≥9%) or greater (and irrespective of self-monitoring blood glucose frequency) was 18.6 mmol/mol [38, 39]. Assuming a correlation between repeated measures of 0.7, a sample size of 58 (29 per group) would provide 80% power to detect a difference in mean changes for HbA1c of 1% (10.93 mmol/mol) using a two-sided test at the 0.05 level. This would be considered a clinically important difference, of a similar magnitude to other proven technologies such as insulin pumps or CGM [40]. To account for a small amount of missing data and loss to follow-up (anticipated to be < 10%), we will recruit a sample size of 64 (32 participants per group) at baseline. Reasons for non-retention of participants (i.e., consent withdrawn, moving outside of the study DHBs, or lost to follow-up) will be recorded and shown in a CONSORT flow diagram (Fig. 1).

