#### Study groups

##### Usual care (waitlist control) group

Participants allocated to the waitlist control group will receive standard diabetes care from their usual provider. In New Zealand, these clinics are attended regularly (usually a minimum of every 3 months) to provide diabetes care by a multi-disciplinary team (i.e., paediatric or adult endocrinologist/diabetologist (depending on patient age), diabetes nurse specialist, dietician, psychologist/social worker). Participants will continue self-monitoring their blood glucose levels with their usual glucose meter per recommendations from their clinical care team. All other aspects of diabetes care will remain with their usual clinical care facility and will be in no way altered by the study team. No additional diabetes care, support, or advice will be provided by the study team making the provision of the FreeStyle Libre (Abbot Diabetes Care, Witney, Oxon, UK) FGM system, along with instruction in its use, the only difference between intervention groups. To maximise study retention in the control group, participants allocated to this group will receive FGM for 6-months at the completion of their 6-month follow-up study visit.

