The main analyses will follow a modified intention- to-treat principle with all participants analysed in the group to which they were randomised, regardless of actual sensor wear. Per protocol analyses will be also be investigated by including only those from the FGM group who scanned at least 12 out of 14 days in the two weeks prior to the 6-month study visit and excluding any participants from the SMBG group who used FGM at any time during the study. All models will include variables used in minimization [59].

Any missing HbA1c values will be imputed using multiple imputation with chained eqs. (100 imputations after at least 100 burn-ins) and with the imputation model including: gender, HbA1c status at baseline as well as values of that variable from other time points, insulin regimen, frequency of self-monitored glucose (capillary or interstitial) and socioeconomic status. If missing data exceeds 10%, plausible scenarios involving informative missing data will be investigated to explore the robustness of findings.

Statistical analyses will be performed using R 3.5.2 or Stata 15.1 software (or later versions) with two-sided *p* < 0.05 considered significant. To maintain the integrity of the study, statistical analyses will be performed by the biostatistician blinded to group allocation.

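### The per-protocol rule excludes controls who used FGM at any time in a 12-month study in which all controls are offered FGM at month 6; the scanning threshold also selects on post-randomisation behaviour in the FGM arm only

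*Protocol article*

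**What the plan says.** The rule appears twice in the protocol article. The tertiary objectives (Aim, objectives and hypotheses) plan to repeat "all of the primary and secondary analyses using participants from the FGM group who scanned at least once per day 12 days out of 14" before the 6-month visit. Statistical analysis restates this condition, again tied to that visit, as "including only those from the FGM group who scanned at least 12 out of 14 days in the two weeks prior to the 6-month study". Both sections then add the same condition for controls: "excluding any participants from the SMBG group who used FGM at any time during the study".

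Study design fixes the time frame: "Once enrolled, the total study period is 12 months for each participant". In the second half, "the control group will cross over and receive a 6-month FGM intervention". The section on the usual care group gives the timing: "participants allocated to this group will receive FGM for 6-months at the completion of their 6-month follow-up study visit". The Discussion also describes a 12-month study made up of a 6-month randomised trial and a 6-month continuation.

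The tertiary objectives describe the exercise as "a per protocol analysis with potential confounding by characteristics associated with compliance". They then play this down, on the ground that everyone enrolled has a recent history of poor control and so probably tested little at baseline.

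**The concern.** There are two separate problems.

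First, the exclusion window is wrong for the design. If the study is 12 months long and controls are supplied with FGM for the last six, then a control who follows the protocol to the end has used FGM during the study. The rule as worded classes that participant as a deviator. A programmer who applies it to the complete dataset would delete the comparator from every per-protocol result.

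Second, even with the window corrected, the two arms are filtered differently. FGM participants must show diligent scanning shortly before the endpoint is measured. Controls need only have stayed off FGM; no level of testing is required of them. If people who scan reliably also tend to improve more for reasons unrelated to the device, the comparison favours FGM. A per-protocol estimate may be read by clinicians or funders as the effect in people who actually use the device, so its limits should be stated correctly.

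**Working it through.** **Inputs from the protocol (Sample size).** The SD of HbA1c "was 18.6 mmol/mol", the correlation between repeated measures is 0.7, the target difference is 10.93 mmol/mol, the test is two-sided at 0.05, and there are 29 evaluable and 32 recruited per group.

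**The plan's own figure.** SD of change = 18.6 × √(2 × (1 − 0.7)) = 14.41. With 29 per group the noncentrality is 10.93 / (14.41 × √(2/29)) = 2.89, and the noncentral t gives power 0.810. At 28 per group it gives 0.796. So 29 per group is the smallest size reaching 80%, and the plan's figure reproduces.

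**Literal reading of the exclusion.** The rule excludes on FGM use at any time in the study; the study is 12 months; FGM is offered to all controls at month 6.

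- If all controls are retained and accept FGM, 32 of 32 are excluded (29 of 29 on the evaluable count). No between-group contrast can be estimated.
- If 5–10% of 29 decline (an assumption; the protocol gives no rate), about 1 to 3 controls remain. Against 29 FGM participants, power for 10.93 mmol/mol is 0.11 to 0.23.
- The controls left would be those who declined FGM or left before month 6, which is a poor comparator in any case.

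**Window ended at the 6-month visit.** Up to 29 evaluable controls remain. Power then depends on how many of the 29 FGM participants meet the scanning rule (shares assumed):

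| Share meeting rule | FGM n | Control n | Power |
|---|---|---|---|
| 100% | 29 | 29 | 0.810 |
| 80% | 23 | 29 | 0.759 |
| 70% | 20 | 29 | 0.725 |
| 60% | 17 | 29 | 0.681 |
| 50% | 14 | 29 | 0.624 |

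**One-sided selection with no device effect.** Suppose a normal adherence score has correlation r with HbA1c improvement, and only the top fraction p of the FGM arm is kept. The contrast shifts by r × 14.41 × φ(z)/p, where z is the cut-off for the top fraction p and φ is the standard normal density.

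| p (assumed) | r (assumed) | φ(z)/p | Shift, mmol/mol |
|---|---|---|---|
| 0.8 | 0.2 | 0.350 | 1.01 |
| 0.6 | 0.3 | 0.644 | 2.78 |
| 0.4 | 0.5 | 0.966 | 6.96 |

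Similar baseline testing does not enter this calculation. Randomisation already balances baseline in expectation; the shift comes from selecting on behaviour six months later.

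**The case against.** The strongest reply is that nobody would apply the rule literally. The per-protocol set serves the primary and secondary analyses, which concern month 6. The FGM criterion in the same sentence is tied to the 6-month visit. Controls receive FGM only once that visit is complete, and their later data have their own one-group models. The word study is also used in Study design for the 6-month randomised comparison. This stands as evidence of intent. It does not make the wording safe: the secondary objectives refer to the 6-month trial period, whereas the exclusion refers to the study, whose stated length is 12 months.

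A reader might infer that the trial loses its control arm for its main results. The documents do not support that. The main analyses keep all participants in their randomised group regardless of sensor wear, and only a tertiary repeat is touched.

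A reader might also infer that the confounding was overlooked, or that the comparison must favour FGM even if the device does nothing. Neither holds. The protocol names the confounding and lists the analysis as exploratory. The direction of bias depends on a positive link between adherence and improvement. The Background reports observational associations of more frequent testing and scanning with lower HbA1c, which makes such a link plausible, but the protocol gives no correlation. Controls are also filtered for keeping to their allocation, and because the protocol sets no testing frequency for them, there is no ready threshold to mirror. The models adjust for gender and HbA1c category, so the SD that matters may be below 14.41. What remains is narrower: the reassurance about baseline testing does not answer selection after randomisation.

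**Conclusion.** The wording defect is certain on the text. As written, the rule contradicts the crossover design and removes up to all 32 controls from the tertiary per-protocol analyses. That is the consequence of the literal words, not the loss to expect if the evident intent is followed.

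The one-sided threshold is a disclosed limitation with an inadequate justification. Its bias cannot be sized from the protocol. About 1 to 7 mmol/mol follows only from assumed compliance of 40–80%, assumed correlations of 0.2–0.5, a normal adherence score and the unadjusted SD of change. The primary analysis and the sample size stand.

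**What to change.** 1. In both the tertiary objectives and Statistical analysis, change the control exclusion to participants who *used FGM between randomisation and the 6-month visit*.
2. Delete the remark about similarly low baseline testing, and say instead that the scanning threshold selects on post-randomisation behaviour in the FGM arm only.
3. Report the subset comparison as descriptive.
4. Optionally, add a complier average causal effect with randomisation as the instrument, as a sensitivity analysis. It should not replace the subset comparison without comment. Its exclusion restriction is doubtful at the 12-of-14-day threshold, because someone scanning on 11 days, or heavily until a late lapse, may still benefit. The estimate is roughly the intention-to-treat effect divided by the compliance share: at an assumed 60%, 10.93 / 0.6 = 18.2 mmol/mol, which overstates the benefit if partial users gain too.

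The first three changes cost only wording. The fourth uses data already collected and brings a wider interval and the assumption just described.

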#### Randomisation

Patients who give consent for participation and fulfil the eligibility criteria will be enrolled in the study and randomly allocated by an offsite biostatistician ([name]) in batches using a 1:1 ratio to either the waitlist control (SMBG) group or the intervention (FGM) group. The statistician will be blinded to allocation arm and will use non-informative group codes until all planned analyses are completed. As gender and pre-study HbA1c may significantly affect the primary outcomes, minimisation will be used (based on gender [male, female; HbA1c [75 to < 100 mmol/mol, ≥ 100 mmol/mol; 9.0 to < 11.3%, ≥ 11.3%]) and with a small random component (20%) along with randomly ordering the participants in each batch used to preserve allocation concealment. The study group will be revealed to the participant at the baseline visit after all assessments have been completed.

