### Statistical analysis

Means and standard deviations (SDs) will be reported for continuous variables (i.e., age, diabetes duration, HbA1c, glucose monitoring behaviour, questionnaire scores) that are approximately normally distributed, geometric means and SDs for those that are approximately log-normally distributed, and medians and IQRs otherwise. Categorical variables will be described as the number and percent of participants in each category (i.e., gender, ethnic group, insulin regimen). Adverse events will be categorised by the type of event (e.g., severe hypoglycaemia, DKA, sensor insertion issues, sensor wear issues). The frequency of events will be reported by event category.

A mixed linear model will be used to test the difference in HbA1c, with the primary outcome being at 6-months, between the intervention and control groups, using data from all time points with a random participant effect used to accommodate the repeated measures and a group-time interaction to model differences in longitudinal changes. Changes in number of glucose measurements performed and patient-reported outcome measures (i.e., PedsQL generic core scale, PedsQL diabetes module, HFS, and DTSQs scores) from baseline through to 6 months will be calculated by comparing scores from control and intervention group participants using Poisson (or negative binomial regression if there is evidence of over-dispersion) for count outcomes and linear mixed models for continuous outcomes with all collected data included. Model residuals will be examined along with the distribution of random effects. If residuals are positively skewed, natural logarithmic transformations will be investigated and retained if these improve the satisfaction of model assumptions. Mixed quantile regression will be investigated for continuous outcomes if issues with model residuals remain following such transformations. If HbA1c values of 130 are observed, mixed Tobit models with right censoring at 130 will be used for this outcome instead. All mixed models will use restricted maximum likelihood (REML) estimation for the variance components.

Some secondary analyses, such as those involving the wait-list control after they cross over, will only include participants from one group and so group (and group-time interaction) terms will not be included in these models.

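### The primary HbA1c contrast is in effect a raw change-score comparison; constraining the arms to a common baseline mean would gain modest precision at almost no cost

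*Protocol article*

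**What the plan says.** All references are to the protocol article.

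- **Outcome measures** defines the primary outcome as the between-group difference in HbA1c change at 6 months. Table 2 lists baseline among the HbA1c time points.
- **Statistical analysis** specifies a linear mixed model on all time points, with a random participant effect and "a group-time interaction to model differences in longitudinal changes". It says that one-group analyses drop both the group and the group-time terms, which implies that two-group models contain both.
- **Statistical analysis** also states "All models will include variables used in minimization". Under **Randomisation** these are gender and "HbA1c [75 to < 100 mmol/mol, ≥ 100 mmol/mol; 9.0 to < 11.3%, ≥ 11.3" per cent. No continuous baseline covariate and no equal-baseline constraint is mentioned. Baseline HbA1c otherwise appears only in the imputation model.
- **Sample size** uses a standard deviation that "was 18.6 mmol/mol", then: "Assuming a correlation between repeated measures of 0.7, a sample size of 58 (29 per group) would provide 80% power" for "a difference in mean changes for HbA1c of 1% (10.93 mmol/mol) using a two-sided test at the 0.05 level". Allowing for losses, "we will recruit a sample size of 64 (32 participants per group) at baseline".

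**The concern.** A reader of the covariate sentence would expect the primary estimate to be adjusted for baseline HbA1c, at least by band. In the model described it is not. A covariate that is constant over time shifts every visit of a participant equally, so it drops out of a difference between visits. What remains is the change score, which subtracts the whole baseline value although the assumed correlation of 0.7 calls for subtracting only part of it. The estimate is noisier than it need be, and it over-corrects any chance baseline difference left within the two HbA1c bands. The lower band alone spans 25 mmol/mol, more than one standard deviation. With 64 participants, precision that costs nothing is worth having.

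**Working it through.** **Inputs.** From Sample size: SD 18.6 mmol/mol, correlation ρ = 0.7, difference 10.93 mmol/mol, two-sided 5% test, 29 per group. From Randomisation: 1:1 minimisation with a 20% random component and an HbA1c cut at 100 mmol/mol. Assumed for simulation: normally distributed HbA1c with mean 95 mmol/mol and equal correlation between visits.

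**1. The plan's own figure.** SD of change = 18.6 × √(2 × (1 − 0.7)) = 14.41, variance 207.6. With the noncentral t distribution, 29 per group is the smallest number reaching 80%, with power 81.0%. A 6-month-only comparison would need 47 per group and a baseline-adjusted one 25. Only the change-score formula gives 29. Losses of 9% give 58/0.91 = 63.7, hence 64.

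**2. What the model estimates.** Write the mean at visit t as μ + γ(t) + α·group + δ(t)·group + β₁·gender + β₂·band, with δ = 0 at baseline. Then δ(6 months) is the 6-month group difference minus the baseline group difference. The β terms are the same at both visits and cancel. In 600 simulated complete-data trials fitted by REML at baseline, 3 and 6 months, this estimate equalled the raw difference in mean change to within 1e-12. That held with HbA1c entered as a two-level band and also as a continuous main effect, so adding continuous baseline as a main effect to this model would gain nothing.

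**3. Gain by formula, ignoring minimisation.** Using baseline optimally, variance = (1 − 0.7²) × 18.6² = 0.51 × 345.96 = 176.4, SD 13.28. The ratio is 176.4/207.6 = 0.85, which is (1 + ρ)/2. At 29 per group the standard error falls from 14.41 × √(2/29) = 3.78 to 13.28 × √(2/29) = 3.49. Power rises from 81.0% to 86.8%, and the difference detectable with 80% power falls from 10.8 to 9.9 mmol/mol.

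**4. Gain allowing for minimisation.** Balancing on the band already limits baseline differences between arms. With arms balanced within band, the simulated SD of the estimate was 3.59 for the planned contrast, 3.44 for baseline as covariate and 3.43 for a common baseline mean. (3.44/3.59)² = 0.918, about 8% less variance; power was 0.87 against 0.90. Simulation of the minimisation itself gave about 6% less variance and power of about 82% against 86-87%.

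| ρ | Variance cut, formula | Power, formula | Variance cut, with minimisation | Power, with minimisation |
|---|---|---|---|---|
| 0.5 | 25% | 59% to 72% | about 11-12% | 59% to 70% |
| 0.6 | 20% | 69% to 78% | about 8% | not run |
| 0.7 | 15% | 81% to 87% | about 6-8% | 82% to 86-87% (0.87 to 0.90 in the first simulation) |
| 0.8 | 10% | 94% to 96% | about 2-3% | 94% to 95% |

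**The case against.** The strongest reply is that nothing here is wrong. The stated outcome, the model and the sample size all concern a difference in changes, and they agree. The contrast is unbiased and the stated power is reproduced. That stands, so a reader who inferred a biased or underpowered primary analysis would be going beyond the document.

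A reader might also take the 15% as the size of the loss. The formula assumes simple randomisation, whereas this trial minimises on HbA1c band, which recovers roughly half of it. Nor does anything in the article suggest that the correlation is below 0.7, so the larger gains at 0.5 and 0.6 are a sensitivity range and not a forecast.

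The reading of the model is partly inferred. The article does not say outright that baseline is a response, or how HbA1c is coded as a covariate. The first follows from the use of all time points, the change outcome and the group terms; the second does not affect the contrast. The section also speaks of testing the difference in HbA1c at 6 months. If that meant the 6-month group difference from the same model, the simulated SD would be larger still, at 4.02.

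Finally, moving baseline to the covariate side sits badly with the censoring rule. Readings above 130 are recorded as 130, and any value of 130 triggers a Tobit model. A censored baseline used as a covariate would enter as if exact. This bears on the choice of remedy but does not remove the gain.

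**Conclusion.** This is an optional improvement and not a defect. On the natural reading, the promised adjustment for the minimisation variables leaves the complete-data primary contrast unchanged, and baseline HbA1c is used less efficiently than it could be. At the plan's correlation the realistic gain is about 6-8% in variance and 3-5 power points at 29 per group.

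The size rests on the plan's SD and correlation, on roughly normal HbA1c with equal correlation between visits, and on the minimisation factor tracking the baseline-visit value. The article calls that factor pre-study HbA1c; if it differs from the baseline value, balance is looser and the gain moves towards the formula figure. The exact identity with the raw change holds for complete data and is approximate with missing values or under the Tobit model.

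**What to change.** Keep baseline HbA1c as a response and constrain the arm means to be equal there: omit the group main effect and keep a group term at each follow-up visit. Retain gender and HbA1c band as covariates, and name the 6-month adjusted mean difference as the primary estimate. This form stays compatible with the Tobit rule, because a baseline of 130 is still treated as censored.

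One detail needs care. The band is cut from HbA1c itself, so adjusting for it narrows the baseline spread more than the follow-up spread. A single random participant effect assumes equal spread at all visits and could then understate the 6-month standard error. Let variances and covariances differ by visit, or use participant-clustered robust standard errors.

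If no baseline value is censored, a near-equivalent is to model the 3- and 6-month values with continuous baseline HbA1c by visit as a covariate, at a cost of two slope parameters.

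Either way the cost is plan wording, settled before unblinded data are seen. No new data are needed and the sample size can stand.

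### The article does not say whether the primary 6-month HbA1c estimate comes from observed values or from multiply imputed values

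*Protocol article*

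**What the plan says.** All of this is in the protocol article.

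- **Aim, objectives and hypotheses.** The primary objective carries the gloss that "the primary analysis will be on a modified intention to treat basis, using all available data". Nothing else in the article explains 'modified'.
- **Statistical analysis, model.** HbA1c is compared between groups at 6 months with a mixed linear model, "using data from all time points with a random participant effect used to accommodate the repeated measures", plus a group-time interaction. Variance components are estimated by REML. A mixed Tobit model replaces it if readings at the analyser's ceiling of 130 occur. Imputation is not mentioned here.
- **Statistical analysis, analysis principle.** "The main analyses will follow a modified intention- to-treat principle with all participants analysed in the group to which they were randomised". Also: "All models will include variables used in minimization".
- **Statistical analysis, missing data.** "Any missing HbA1c values will be imputed using multiple imputation with chained eqs", with 100 imputations. The listed predictors are gender, HbA1c at baseline and at other time points, and "insulin regimen, frequency of self-monitored glucose (capillary or interstitial) and socioeconomic status". Randomised group is not on the list. The only missing-data work labelled as a robustness check is this: "If missing data exceeds 10%, plausible scenarios involving informative missing data will be investigated to explore the robustness of findings".

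**The concern.** A likelihood-based mixed model handles missing visits under a missing-at-random assumption without filling them in. Imputing first and pooling is a different estimator of the same contrast. It has its own model for the missing values and, here, uses variables that are not named as terms of the mixed model. The article supports both and calls neither primary nor supportive.

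The trial has one primary contrast, tested two-sided at 0.05 in 64 participants. If the data basis is left open, a borderline result could depend on a choice made after both versions have been seen. The statistician's use of coded groups lowers this risk but does not remove it, because p values are visible under coded labels.

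**Working it through.** **1. The plan's own figure.** Inputs from Sample size: SD 18.6, correlation 0.7, difference 10.93, 80% power, two-sided 0.05.
- SD of change = 18.6 × √(2 × (1 − 0.7)) = 14.41.
- Normal approximation: 2 × (14.41 × (1.960 + 0.842) / 10.93)² = 27.3, so 28 per group.
- With the t distribution, power is 79.6% at 28 per group and 81.0% at 29. The stated 29 per group (58) is reproduced.
- Recruiting 64 allows 1 − 58/64 = 9.4% loss, in line with the stated expectation of under 10%.

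None of this depends on how missing HbA1c is handled, so no stated figure changes.

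**2. Who is analysed.** Table 2 schedules HbA1c at baseline for everyone, and Randomisation says the group is revealed only after the baseline assessments. A mixed model using all time points therefore keeps practically every randomised participant, as imputation does.

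**3. Expected shift if imputation omits group.** Assume 6 of 64 values missing at 6 months, completely at random, the 3-month value seen, and an effect at 3 months equal to that at 6 months.
- Variance of the 3-month value given baseline, group ignored: 18.6² × (1 − 0.49) + 10.93²/4 = 176.4 + 29.9 = 206.3.
- Covariance with the 6-month value: 18.6² × (0.7 − 0.49) + 29.9 = 72.7 + 29.9 = 102.5.
- Slope = 102.5 / 206.3 = 0.50, so an imputed value carries about half the group effect.
- Shrinkage = (6/64) × (1 − 0.50) × 10.93 ≈ 0.5 mmol/mol. If the 3-month value is missing too, the bound is (6/64) × 10.93 ≈ 1.0.

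**4. Simulation.** 64 participants, SD 18.6, correlation 0.7, missing completely at random, HbA1c values as the only imputation predictors. The difference of 7.6 is a borderline case, close to the smallest significant difference with 29 per group: 2.00 × 14.41 × √(2/29) = 7.6.

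| True difference | Missing at 6 months | Mean estimate, observed v imputed | Power, observed v imputed | Opposite verdicts at 0.05 | Same, with group in imputation |
|---|---|---|---|---|---|
| 10.93 (600 trials) | 6 of 64 | 10.81 v 10.26 | 81% v 78% | 3.2% | 2.0% |
| 10.93 (300 trials) | 6 of 64 | 11.0 v 10.5 | 83% v 82% | 1% | 1% |
| 7.6 (600 trials) | 6 of 64 | not reported | not reported | 6.8% | 2.5% |
| 7.6 (300 trials) | 6 of 64 | 7.7 v 7.3 | 57% v 49% | 7% | 1% |
| 7.6 (300 trials) | 13 of 64 | 7.9 v 6.9 | 52% v 39% | 14% | 5% |

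The 600-trial rows also had 4 values missing at 3 months. Imputations numbered 30 (600 trials) or 20 (300 trials), against the planned 100. The gap of 10.81 − 10.26 = 0.55 agrees with step 3.

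A smaller run (40 trials per setting, true difference 8) had group and an auxiliary that drives missingness in the imputation model. The mean absolute difference was 0.2 to 0.5 at about 9% missing (largest 2.0, standard error about 3.7) and 0.5 to 0.8 at about 20% (largest 3.2). Verdicts differed in 1 to 3 of 40 trials per setting.

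A further run at about 9% missing gave mean absolute differences of 0.3 to 0.65, and about 0.3 with group added. Without group, mean estimates fell from 10.7 to 10.1 and from 7.5 to 7.1, the latter with power falling from 55% to 42%. The shift was smaller when monitoring frequency stood in for group.

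**The case against.** The strongest reply is that there is only one pipeline. The Statistical analysis section runs in order through model, principle, covariates and then an unconditional imputation rule, so the ordinary reading is to impute, fit and pool. The model paragraph speaks of data from all time points, which describes the repeated-measures structure; it does not restrict the fit to observed values. Using all available data may mean only that nobody is dropped for non-use, and imputation also uses all available data. Imputation can exploit auxiliaries that the mixed model does not list. A condensed article may leave the linking sentence to the full plan.

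Much of this stands. The observed-data side rests mainly on the wording in the objectives, and neither method is invalid. What remains is that the single pipeline is never stated, fits the objectives' wording less naturally, and leaves 'modified' unexplained, since imputing every gap would give a full intention-to-treat analysis. The point is not a missing detail: two statements about the primary analysis exist, and a full plan could follow either and claim agreement with the article.

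A reader might also infer that the two routes analyse different participants, since one statement speaks of available data and another says "with all participants analysed in the group to which they were randomised". The baseline HbA1c schedule does not support that.

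**Conclusion.** The point holds as an unfixed primary estimator, not as a large expected bias. A reader might infer that the article prescribes two rival primary analyses with materially different results. The documents do not support that: one pipeline is a possible reading, and at the anticipated loss of under 10% the two results will usually be close.

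At about 9% missing, the average difference was about 0.2 to 0.65 mmol/mol, and significance verdicts differed in about 1% to 7% of simulated trials, towards the upper end when the true effect was borderline. At about 20% missing they differed in up to 14%. The systematic part of the gap comes from leaving group out of the imputation model, which pulls the effect slightly towards zero. With group included, verdict disagreement in the missing-completely-at-random runs was 1% to 2.5% at about 9% missing and 5% at about 20%.

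These figures assume exchangeable correlation, mostly missingness completely at random, and HbA1c-only imputation in the main runs. Monitoring frequency is a listed predictor and may partly stand in for group, so the real attenuation could be smaller. The runs are modest in size, and the disagreement rates are indicative only.

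**What to change.** In Aim, objectives and hypotheses and in Statistical analysis, state that the primary 6-month estimate and p value come from the mixed model already specified (or its stated Tobit version), fitted to observed HbA1c values without imputation, in all randomised participants with at least one HbA1c value. Label multiple imputation as a sensitivity analysis that does not replace the primary result. Define 'modified' as that analysis set, or drop the word.

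If the sponsor prefers pooled imputation as primary, that also settles the matter. The text should then say that the mixed model is fitted to the imputed data sets and pooled, and the imputation model should include randomised group and its relation to time.

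The cost is one or two sentences, with no new data and no change in sample size. The small downside of the first option is that insulin regimen, monitoring frequency and socioeconomic status then inform only the sensitivity analysis.
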